### **Estimation of the incidence of COVID-19 cases in the population in the Paris Metropolitan area.**

We will consider the cohort of patients arriving at the emergency department over time and the proportion of positive tests for COVID-19. The incidence rate among patients during a given week will be calculated as the ratio between the number of positive tested patients during that week and the total number of patients admitted to the emergency room during that week. The ratio will first be calculated by age group (for example: 0-18; 19-40; 40-64; 65+) and by sex, and weighted by the proportion of the general population of the strata in the region. The confidence interval of the estimate is obtained using a rescaled Poisson distribution (DKES estimator). The results will be compared to those from an age-stratified mathematical that has already been validated and used to estimate the impact of lockdown during the first wave and for the proposal of exit strategies. Calibrated on the number of hospitalisations in the region, this model allows us to estimate the total number of cases and therefore the detection rate of virological monitoring in region .

IPLESP, SUMO, INSERM will be in charge of the analysis.

## **1.2 Hypotheses for calculating the required number of subjects**

The estimate of the sample size is based on the comparison of 2 proportions (control group vs intervention group) using a Fisher's exact test, with, for the control group, a proportion of patients tested positive for SARS-CoV-2 among the enrolled patients of 0.1% and a proportion of 0.2% for the intervention group, bilateral  $\alpha=5\%$  and  $\beta=10\%$ .

The proportion of the control group was set using the incidence rate of SARS-CoV-2 among the general population in the Paris Metropolitan area. The incidence rate was 0.12% on 26/11/2020. It was estimated that the proportion of 0.10% was close to the baseline proportion of new SARS-CoV-2 positive cases among a flow of patients in the emergency department with usual screening practices.

The correlations used are extracted from the DICI-VIH study (intra-cluster correlation:  $\rho=0.00014$ , correlation between-cluster:  $\rho_{12}=0.00009$ ). The calculation was performed with SAS software (version 9.4; SAS Institute, Inc., Cary, NC) and resulted in the need to enrol 104,000 patients , i.e. a total enrolment period of 2 months in 18 emergency departments (including 1 month intervention, 1

|                        |              |
|------------------------|--------------|
| Study                  | DEPIST-COVID |
| Promotion/gestion code | APHP201625   |
| Study coordinator      | [name]   |

month control and wash-out). Simulations were performed using different incidence rates and worst case scenario involving the largest number of patients to be enrolled, i.e. 104,000 patients.

### 1.3 Method for taking into account missing, unused or invalid data

Missing values for the primary outcome will not be replaced.

Missing values from the questionnaires will not be replaced; this strategy will be reassessed according to the proportions of missing values obtained.

### 1.4 Selection of populations

The primary analysis will be performed according to the intent-to-treat (ITT) principle. The primary outcome, i.e. proportion of patients tested positive for SARS-CoV-2 among the flow of consulting adults, will be evaluated at the end of the 15-day  $\pm$  10 follow-up period, based on the patient's medical record.

For primary and secondary outcomes, data will be extracted from:

- patient self-administered questionnaire data (DEPIST-COVID),
- from virological confirmation data collected from referring physicians,
- aggregated data from emergency department flows,
- and data collected using locally used software (URQUAL, ORBIS, SUMD, for example).

### 1.5 Summary of the main changes since the validation of the protocol

For the primary endpoint, the analysis plan was revised to mention that the incidence of SARS-CoV2 or the evolution of the epidemic over time could be taken into account and that fixed variables could be added to the model. The period x strategy interaction is usually added as a fixed variable and this was corrected from the initial analysis plan.

The analysis plan was revised for the secondary endpoints due to data that could not be collected. Symptoms, exposure factors and follow up data in the COVISAN monitoring system were not collected for patients tested outside of DEPIST-COVID screening during the intervention period and for patients tested during the control period. Data were also not collected for close contact persons. Objectives and analysis plan were adapted accordingly.

|                 | Coordinator / biostatistician                                                       | Coordinator data management and statistic URC-Est                                    |
|-----------------|-------------------------------------------------------------------------------------|--------------------------------------------------------------------------------------|
| First name Name | [name]                                                                      | [name]                                                                   |
| Date            | 21/04/2022                                                                          | 22/04/2022                                                                           |
| Signature       | [figure not shown] | [figure not shown] |

|                               |              |
|-------------------------------|--------------|
| Study                  | DEPIST-COVID |
| Promotion/gestion code | APHP201625   |
| Study coordinator      | [name]   |

## Changes to the analysis plan

### **Primary endpoint analysis**

The primary outcome will be analysed using a generalised linear mixed model (Poisson distribution or any other distribution adapted to the data) with the centre as a random intercept, the centre-by-period interaction as random effect and the strategy, the period and the incidence rate-by-period interaction as fixed effects. The logarithm of the number of patients will be included as an offset term in the model.

The period will be modelled as weekly (1 to 15).

Patients considered non-positive for SARS-CoV-2 will be patients not tested, patients tested negative or with an undeterminate result and patients tested positive with a known SARS-CoV2+ status for less than 3 months.

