##### Primary endpoint analysis

The primary endpoint is the proportion of patients tested positive for SARS-CoV-2 amongst the flow of consulting adults. The denominator is a number of patients in the emergency departments (and not the number of tests performed).

Patients considered positive for SARS-CoV-2 will be those with a positive test result and whose SARS-CoV2+ status is not known. Patients considered non-positive for SARS-CoV-2 will be patients not tested, patients tested negative or with an undeterminate result and patients tested positive with a known SARS-CoV2+ status.

The primary analysis will be performed according to the intent-to-treat (ITT) principle. The primary outcome will be analysed using a generalised linear mixed model (Poisson distribution or any other distribution adapted to the data) with the centre as a random intercept and the strategy, the period and the period x strategy interaction as fixed effects. The incidence of SARS-CoV2 or the evolution of the epidemic over time will be taken into account if appropriate. Fixed variables could be added to the model if appropriate.

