# Appendix I. Primary outcome modeling, sensitivity analyses, and intercluster and intracluster correlation coefficients

## 1. Final model

The following models were compared using likelihood ratio tests:

- A model including the center as a random intercept, the center-by-weekly period interaction as a random effect, as well as the strategy (intervention vs. control) and the weekly period as fixed effects.
- A model including the same variables (Model a) and the community incidence rate for SARS-CoV-2 as a fixed effect.
- A model including the same variables (Model b) and the community incidence rate-by-weekly period interaction.

The selected model was **Model c**.

Table I1. Coefficient estimates from the generalized linear mixed model with a Poisson distribution including the center as a random intercept, the center-by-weekly period interaction as a random effect and the strategy, weekly period and community incidence rate-by-weekly period interaction as fixed effects (SAS PROC Glimmix)

| Variable                                              | Coefficient | Standard error | t test | p value | Relative risk | (95% Confidence interval)
relative risk |
|-------------------------------------------------------|-------------|----------------|--------|---------|---------------|--------------------------------------------|
| Strategy                                              | 0.02        | 0.04           | 0.48   | 0.63    | 1.02          | (0.94 to 1.11)                             |
| Weekly period                                         | -0.09       | 0.02           | -4.45  | <.0001  |               |                                            |
| Community incidence rate                              | 0.00        | 0.00           | -0.75  | 0.46    |               |                                            |
| Community incidence rate-by-weekly period interaction | 0.00        | 0.00           | 5.33   | <.0001  |               |                                            |

  

| Covariance                   | Coefficient | Standard error |
|------------------------------|-------------|----------------|
| Center                       | 0.07        | 0.03           |
| Center-by-period interaction | 0.00        | 0.00           |

The variability among centers was estimated as small (0.07) compared to the associated standard error (0.03).

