The ratio of the 'Generalized Chi-Square statistic' and its degrees of freedom was 1.17 and close to 1. The scaled Pearson statistic for the conditional distribution was similar (1.17). These arguments are not in favour of an overdispersion of the data.

Significant weekly period effect ( $p < 0.0001$ ) and community incidence rate-by-weekly period interaction ( $p < 0.0001$ ) were identified.

Table I2. Significant random effects

| Variable                     | Center    | Coefficient | Standard error | t test | p value |
|------------------------------|-----------|-------------|----------------|--------|---------|
| Intercept                    | Center 1  | -0.36       | 0.14           | -2.61  | 0.01    |
| Center-by-period interaction | Center 11 | 0.05        | 0.02           | 2.48   | 0.02    |
| Intercept                    | Center 13 | 0.30        | 0.15           | 2.02   | 0.05    |
| Intercept                    | Center 5  | 0.31        | 0.14           | 2.17   | 0.04    |
| Intercept                    | Center 6  | 0.33        | 0.13           | 2.59   | 0.01    |
| Intercept                    | Center 8  | -0.37       | 0.14           | -2.72  | 0.01    |

According to the random parameters of the final model, the intracluster variability was not negligible. Significant differences were observed in 5 centers. Given the multiplicity of the tests, the interpretation is limited.

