## 2. Sensitivity analyses

Table I3. Analysis considering a binarized period (0/1)

| Variable     | Coefficient | Standard error | t test | p value | Relative risk | (95% Confidence interval)
relative risk |
|--------------|-------------|----------------|--------|---------|---------------|--------------------------------------------|
| Intervention | -0.02       | 0.07           | -0.25  | 0.80    | 0.98          | (0.84 to 1.15)                             |

  

| Covariance                   | Coefficient | Standard error |
|------------------------------|-------------|----------------|
| Center                       | 0.08        | 0.04           |
| Center-by-period interaction | 0.03        | 0.02           |

Table I4. Analysis including variables used for randomization (screening equipment in emergency departments and flow in emergency departments)

| Variable     | Coefficient | Standard error | t test | p value | Relative risk | (95% Confidence interval)
relative risk |
|--------------|-------------|----------------|--------|---------|---------------|--------------------------------------------|
| Intervention | 0.02        | 0.04           | 0.53   | 0.60    | 1.02          | (0.94 to 1.11)                             |

  

| Covariance                   | Coefficient | Standard error |
|------------------------------|-------------|----------------|
| Center                       | 0.06        | 0.03           |
| Center-by-period interaction | 0.00        | 0.00           |

Table I5. Analysis including strategy \* week\_since\_roll\_out interaction

| Variable                     | Coefficient | Standard error | t test         | p value | Relative risk | (95% Confidence interval)
relative risk |
|------------------------------|-------------|----------------|----------------|---------|---------------|--------------------------------------------|
| Intervention                 | -0.02       | 0.07           | -0.28          | 0.78    | 0.98          | (0.85 to 1.13)                             |
|                              |             |                |                |         |               |                                            |
| Covariance                   |             | Coefficient    | Standard error |         |               |                                            |

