### 3. Intercluster and intracluster correlation coefficients

The intercluster correlation coefficient  $\rho_{12}$  and intracluster correlation coefficient  $\rho$  were calculated *a posteriori* following the Donner formula [1]. Small correlation values were found:

$$\rho_{12} = 0.0012$$

$$\rho = 0.0035$$

The basic assumption for the final model (the intercluster correlation was zero) was supported by the data.

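### The primary model has no random effect for the centre x crossover-period, so the standard error of the strategy effect is too small if step-like variation between an ED's two periods remains after adjustment

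*Combined protocol and SAP*

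**What the plan says.** The primary model changes over the course of the documents.

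- **Protocol, section 13.2:** strategy fixed, centre as random intercept, and a centre x strategy random effect. With two periods per centre and one strategy in each, that last term is a centre x crossover-period effect.
- **Final SAP, section 1.1:** "with the centre as a random intercept and the strategy, the period and the period x strategy interaction as fixed effects". Section 1.5 presents the fixed interaction as a correction.
- **Changes to the analysis plan:** a centre random intercept, "the centre-by-period interaction as random effect and the strategy, the period and the incidence rate-by-period interaction as fixed effects". It adds: "The period will be modelled as weekly (1 to 15").
- **Appendix I, final model:** fitted with "the center-by-weekly period interaction as a random effect". Table I1 gives a strategy SE of 0.04, RR 1.02 (95% CI 0.94 to 1.11), and a centre-by-period variance printed as 0.00.
- **Appendix I, Table I3:** "Analysis considering a binarized period (0/1"). The centre-by-period variance is 0.03 (SE 0.02), the strategy SE 0.07, and the RR 0.98 (0.84 to 1.15).

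On the adequacy of the model, Appendix I says of the dispersion statistics (1.17): "These arguments are not in favour of an overdispersion of the data". Of the correlations it says: "The basic assumption for the final model (the intercluster correlation was zero) was supported by the data".

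**The concern.** The site is randomised to an order of two periods (protocol sections 5.1 and 5.3). The strategy effect is then estimated by comparing the two periods of the same ED. Its error must include how far an ED's positivity moves between those periods for reasons other than strategy. More patients per ED do not reduce that component; only more EDs or more crossovers do.

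Once period means calendar week, the term called centre-by-period no longer carries this component. What is at stake is the width of the primary confidence interval. In a trial with a null result, that interval is the main finding: it says how large a gain from screening has been ruled out.

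**Working it through.** **1. What the fitted term is.** Table I1 has one coefficient for weekly period (-0.09), so week entered as a straight line. Table I2 lists one centre-by-period coefficient for centre 11 (0.05), with no week index. The term is a centre-specific linear slope on week. Had week been categorical, it would be a centre-week effect, again not a centre x crossover-period effect.

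**2. Reproducing the printed standard errors.** SE = ln(upper/lower)/(2 x 1.96).
- Table I1: ln(1.11/0.94)/3.92 = 0.042 (printed 0.04).
- Table I3: ln(1.15/0.84)/3.92 = 0.080; with t on 16 df (2.12) it is 0.074 (printed 0.07).

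**3. Standard error by source.** Events come from Table H1: 2,084 control and 1,859 intervention.
- Poisson error only: sqrt(1/2084 + 1/1859) = 0.032.
- Adding an independent centre-period effect of variance v over 18 centres: sqrt(2v/18 + 1/2084 + 1/1859).

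| v | SE |
|---|---|
| 0.01 | 0.046 |
| 0.02 | 0.057 |
| 0.03 | 0.066 |

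The value at 0.03 rounds to Table I3's 0.07. Reading 0.03 instead as the variance of a 0/1 slope gives 0.052, which does not. So Table I3 behaves like a model with a centre-period intercept, while the primary SE of 0.04 is only about 1.3 times pure Poisson error.

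**4. Interval at v = 0.03.** exp(0.02 ± 2.12 x 0.066) = 0.89 to 1.17.

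**5. How the week-slope model behaves.** The weekly data are not in the documents, so Table I1 cannot be refitted. Trials were simulated under assumed conditions: 18 EDs, 5-week periods, staggered starts, no true effect.

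- *Step-shaped centre-period effects.* One set (120 runs per scenario, Table H1 totals, week but no incidence term) gave the following:

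| v | Mean SE, slope model | True SD | Ratio | False positives |
|---|---|---|---|---|
| 0 | 0.033 | 0.029 | no understatement | 7% |
| 0.01 | 0.035 | 0.046 | 0.77 | 13% |
| 0.02 | 0.038 | 0.060 | 0.62 | 24% |
| 0.03 | 0.040 | 0.064 | 0.63 | 23% |

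  A second set, with an epidemic wave and incidence in the model, gave ratios of 0.70, 0.60 and 0.54 and false positives of 16, 22 and 26% at v = 0.01, 0.02 and 0.03. A third gave SE 0.038, 0.042 and 0.045 against SD 0.047, 0.066 and 0.067 (ratios 0.81, 0.64 and 0.67), with false positives of about 10 to 19%.
- *Gradual centre-specific drift.* At a size equivalent to v = 0.03, one set (100 runs) gave SE 0.047, SD 0.057 and 8% false positives. At 0.015 it gave 0.042, 0.043 and 4%. A separate check gave 5 to 7%.
- *Centre x crossover-period intercept.* It held about 4 to 7% under both shapes in the comparison that fitted it to both.

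**6. The two reassurances in Appendix I.** In the second step-shaped set the slope model showed a generalised chi-square/df of 1.08 to 1.20, around the reported 1.17, while understating the SE. The ratio therefore does not detect this problem. The a posteriori correlations are rho = 0.0035 and rho12 = 0.0012, against planned values of 0.00014 and 0.00009. The difference, which a crossover does not cancel, is 0.0023 against 0.00005. Neither value is evidence of zero correlation when clusters hold thousands of patients.

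**The case against.** The strongest reply is that Tables I1 and I3 may describe the same variation. Within a centre, week and crossover period are strongly correlated (r-squared 0.76 over ten consecutive weeks), so week slopes absorb much of a between-period difference. With period midpoints five weeks apart, a slope variance of 2 x 0.03/25 = 0.0024 produces the same between-period difference as v = 0.03, and it would print as 0.00. If EDs drifted gradually, the primary model is nearly right. This stands: the documents cannot separate drift from step.

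The documents also do not say whether Table I3 keeps the community-incidence terms. If it does not, its 0.03 includes epidemic trend that the primary model removes. The variance is itself imprecise (SE 0.02). The correlations carry no stated adjustment for week or incidence. The same applies to the raw counts, such as centre 15 with 19 control and 80 intervention positives over 40 days each: suggestive, but mixed with the epidemic curve.

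A reader might infer from 0.04 against 0.07 that the primary SE is about half of what it should be. The documents do not establish that, because the comparison assumes that all of Table I3's variance survives adjustment and is step-shaped.

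Finally, Table I3's wider interval is already reported, and replacing a primary model after the results is a post-hoc choice. Both are fair. They bear on how the change is labelled, not on whether the term is missing.

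**Conclusion.** The primary model lacks a random effect for the centre x crossover-period, and nothing else in it represents step-like variation at that level. If such variation remains with variance 0.01 to 0.03 after adjustment, the reported SE is roughly 0.55 to 0.8 of the true spread and the type I error about 10 to 25%. If the variation is drift, the understatement is small; if the variance is zero, there is none. Table I3 makes some such variation plausible, but its size needs a refit.

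Two stronger readings are not supported. The result is not overturned: the intervals 0.94 to 1.11, 0.84 to 1.15 and about 0.89 to 1.17 all include 1 and all exclude the planned doubling. Nor is the centre-period the randomised unit; that is the site, and the centre-period is the unit of the contrast. What is in doubt is precision: whether gains above 11% are ruled out, or only those above about 15 to 17%.

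**What to change.** - In the primary endpoint section of the changes to the analysis plan, add a random intercept for centre x crossover period (36 levels) to the centre random intercept. Keep strategy, calendar week, and local incidence with its interaction.
- Use small-sample inference: Kenward-Roger, or t with about 16 df (18 sites in two sequences). The present output appears to use more: Table I6 pairs t = 0.92 with p = 0.36, where 16 df would give 0.37.
- Report that RR and CI as the primary result, or at minimum beside it, with the week-slope model as a sensitivity analysis. State that the change was made after the results were known.
- State which covariates Table I3 includes.
- In Appendix I, section 3, remove the statement that the correlations support a zero value. In section 1, keep the 1.17 figure but do not use it as evidence against centre-period variation.

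The cost is a wording change and one re-run of the mixed model. The downside is a somewhat wider interval; if the added variance is zero, the result barely moves.

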### **Secondary endpoints analyses**

- Factors associated with performing systematic nurse-driven screening will be analysed in patients who had screening offer using a generalised linear mixed model (binomial distribution) with the centre as a random intercept and the patient characteristics as fixed effects.

- The factors associated with new SARS-CoV-2 diagnoses will be analysed using a generalised linear mixed model (binomial distribution) with the centre as a random intercept and patient characteristics as fixed effects.

- The proportions of new SARS-CoV-2 diagnoses through systematic nurse-driven screening overall and per ED, and proportion among all patients tested in EDs, will be compared to the proportion of positive tests among adults tested in the geographical departments of the Paris Metropolitan area using the Miettinen-Nurminen method for risk difference and 95% CI estimations.

[figure not shown]

Coller ici l'étiquette patient

N° DOSSIER :

\_\_\_\_\_  
Centre

\_\_\_\_\_  
Patient

PLEASE FILL OUT THIS QUESTIONNAIRE BY CHECKING THE SQUARE  
CORRESPONDING TO YOUR RESPONSE [figure not shown]

1 You are:

☐ male ☐ female

2 What is your date of birth?

Month Year

3 Do you have symptoms suggestive of Covid-19?

☐ Yes ☐ No

> If yes, please precise:

☐ Fever (>38°C)  
or fever sensation

☐ Cough

☐ Loss of smell

☐ Muscular pain

☐ Unusual fatigue

☐ Breathing difficulty  
(shortness of breath)

☐ Loss of taste

☐ Other

☐ Headache

☐ Sore throat

☐ Diarrhoea

☐ Runny nose

> If yes, date of first symptoms:

Day Month Year

4 What is your postcode?

5 In which country were you born?

☐ France

☐ Other

Please specify your country of birth:

6 Until what age did you study?

years

7 Currently (over the last month):

☐ You work

☐ You do not work

☐ You are seeking employment

☐ You are a student

> If you work:

• Do you work away from home?:

☐ Yes

☐ No

☐ Partially

• Does your occupation expose you to contacts with:

- Members of the public?

☐ Yes

☐ No

- Sick persons?

☐ Yes

☐ No

8 What is your medical coverage:

☐ Social security without supplementary health insurance

☐ CMU (Universal medical cover)

☐ Social security with supplementary health insurance

☐ AME (State medical assistance)

☐ No medical coverage

☐ Other

9 Do you suffer from a chronic disease (diabetes, high blood pressure, angina pectoris, chronic bronchitis, asthma or chronic respiratory disease)?

☐ Yes

☐ No

10 Do you currently smoke cigarettes?

☐ Yes

☐ No

> If yes, do you smoke:

☐ Every day

☐ Occasionally

11 Do you live within a community (in a hostel or student halls for example)?

☐ Yes

☐ No

12 How many people do you currently live with?

people in total

13 Do you have children or students in your home?

☐ Yes

☐ No

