## 2.2 Research hypotheses

Our working hypotheses are that the systematic offering of SARS-CoV-2 screening by rapid emergency tests performed by nursing teams, combined with current diagnostic practice in patients with signs suggestive of Covid-19, would be superior to the control strategy and would allow:

- testing for rare or asymptomatic forms of SARS-CoV-2 infection, particularly in people who may escape other screening schemes, and thus improve the control of SARS-CoV-2 circulation in the Paris Metropolitan area, and compare the positivity rate among asymptomatic patients in the study to that of the Paris Metropolitan area region, while expecting to obtain a higher rate in the emergency department population,

- to study the sociodemographic, behavioural factors and practices associated with SARS-CoV-2 infection in the population tested in the emergency department compared to those captured by other schemes (ComCor and COVISAN),
- estimating, by modelling, the incidence of new SARS-CoV-2 infections in the Paris Metropolitan area during the study period,
- to limit the risks of transmission of persons tested positive through the immediate and direct activation of the COVISAN scheme facilitating the steps of isolation, tracing, and source search.

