| Model without center 12 | 0.02        | 0.04           | 0.44   | 0.66    | 1.02          | 0.94                                       | 1.11 |
| Model without center 13 | 0.03        | 0.04           | 0.68   | 0.50    | 1.03          | 0.94                                       | 1.12 |
| Model without center 14 | 0.02        | 0.04           | 0.46   | 0.64    | 1.02          | 0.93                                       | 1.12 |
| Model without center 15 | 0.00        | 0.04           | 0.02   | 0.98    | 1.00          | 0.92                                       | 1.09 |
| Model without center 16 | 0.03        | 0.04           | 0.69   | 0.49    | 1.03          | 0.95                                       | 1.12 |
| Model without center 17 | 0.02        | 0.04           | 0.42   | 0.67    | 1.02          | 0.93                                       | 1.11 |
| Model without center 18 | 0.03        | 0.04           | 0.76   | 0.45    | 1.03          | 0.95                                       | 1.13 |

A sensitivity analysis was performed at the center level, successively excluding one center from the sample and estimating the parameters of the 18 samples. No center influenced the estimation of the strategy fixed parameter of the model; the response to the intervention did not vary.

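### The pooled excess of nurse-driven ED screening over community screening (Table J1) depends on one of 18 EDs, and no centre-influence check is planned for it

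*Combined protocol and SAP*

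**What the plan says.** Protocol section 2.2 gives this comparison a direction: positivity among asymptomatic patients in the study is set against that of the region, "while expecting to obtain a higher rate in the emergency department population".

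The operative analysis is in Changes to the analysis plan, Secondary endpoints analyses. It takes "The proportions of new SARS-CoV-2 diagnoses through systematic nurse-driven screening overall and per ED" and compares them with community positivity "using the Miettinen-Nurminen method for risk difference and 95% CI estimations". The same item also covers all patients tested in the EDs. No stratification by department, allowance for centre or influence check is specified for either comparison. The two factor analyses listed beside it do carry a random centre intercept.

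Appendix J reports the results: Table J1 pooled, Table J2 by ED, and Table J3 for all tested patients.

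For the primary outcome, Appendix I, section 2 did examine influence: "A sensitivity analysis was performed at the center level, successively excluding one center from the sample and estimating the parameters of the 18 samples". It concluded: "No center influenced the estimation of the strategy fixed parameter of the model". That statement concerns the strategy effect of the primary model only.

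**The concern.** A crude pooled proportion lets one ED with very high positivity set the result for all 18. In Table J2 centre 15 stands at 14.8% against 7.5% in its department, a difference of +7.3 points (3.9 to 11.5). No other ED differs by more than about 3.5 points in either direction. Table J1's lower confidence limit is only 0.01, so little is needed to move it.

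At stake is how the section 2.2 expectation is judged. Table J1 is the pooled evidence for it. If the net excess rests on one site, Table J1 cannot carry a general statement that ED screening of people with few or no symptoms finds more positives than community screening. A reader who has seen Table I6 may also assume that centre influence was ruled out here too.

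**Working it through.** **Inputs.** Table J1: ED 224/4,283; community 156,298/3,400,584. Table J2: diagnoses and screens for each ED, and positives and tests in its department. Centre 15: 49/331 in the ED, 13,585/180,647 in the department. Table J3: ED 3,943/40,367; community 361,089/4,680,491. Table H1: 99 new diagnoses at centre 15 over both periods.

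**Step 1: reproduce the reported figure.** Difference = x1/n1 - x2/n2, with a Miettinen-Nurminen interval.
- 224/4,283 - 156,298/3,400,584 = 5.23% - 4.60% = +0.63 points (0.006 to 1.34). This matches Table J1.
- The 18 rows of Table J2 sum to 224/4,283, and all 18 per-ED differences and intervals reproduce to rounding.

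**Step 2: centre 15's share.** 331/4,283 = 7.7% of screens; 49/224 = 21.9% of diagnoses.

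**Step 3: leave one ED out, Table J1 comparator unchanged.**
- Without centre 15: (224 - 49)/(4,283 - 331) = 175/3,952 = 4.43%, against 4.60%. Difference -0.17 points (-0.77 to 0.52).
- Without any other single ED: +0.32 (centre 11 removed) to +1.05 (centre 16 removed).
- In diagnoses above the Table J1 rate: 224 - 4,283 x 0.04596 = +27.1 in total. Centre 15 gives 49 - 331 x 0.04596 = +33.8; the other 17 EDs give 175 - 3,952 x 0.04596 = -6.6.

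**Step 4: also remove centre 15's department from the comparator.** (156,298 - 13,585)/(3,400,584 - 180,647) = 142,713/3,219,937 = 4.43%. The difference is -0.004 points (-0.60 to 0.68), in effect zero.

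**Step 5: match each ED to its own department.** Expected = sum over EDs of screens x department positivity from Table J2.

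| | Observed | Expected | Difference | Points |
|---|---|---|---|---|
| All 18 EDs | 224 | 201.9 | +22.1 | +0.52 |
| Centre 15 | 49 | 331 x 13,585/180,647 = 24.9 | +24.1 | +7.28 |
| Other 17 EDs | 175 | 177.0 | -2.0 | -0.05 |

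On this basis, removing any single ED other than centre 15 leaves +0.36 to +0.75 points.

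**Step 6: what lies inside the net figure.** Seven other EDs (1, 4, 9, 11, 12, 14, 18) are above their departments, by +29.6 diagnoses in total. Ten are below, by -31.6. So 24.1 + 29.6 - 31.6 = 22.1.

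**Step 7: all tested patients.** Table J3 gives 9.77% - 7.71% = +2.1 points. ED tests by centre are not tabulated for this comparison. The least favourable removal takes out only centre 15's 99 positives: 3,844/40,268 = 9.55%, a difference of +1.8 points.

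Summing the Table J2 community rows is not a usable comparator. They total about 5.45 million tests against 3.40 million in Table J1, so tests in shared departments are counted more than once.

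**The case against.** The strongest reply is that nothing is hidden. The plan asks for per-ED results, Table J2 prints every count and interval with centre 15 in bold, and its note says that three EDs were above their departments. Any reader can derive the missing row, and the endpoint is secondary. This stands as to disclosure. But neither table says that the pooled figure depends on one site, and naming three higher EDs does not convey it.

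A second reply is that Table J1 is fragile anyway: removing any one of centres 1, 4, 5, 6, 9, 11 or 12 also takes the lower limit below zero. True, but in those cases the estimate stays at +0.32 or more. Only removing centre 15 brings it to about zero. A third is that dropping the most extreme site after seeing the data is selective. That is why all 18 removals belong in the table and the main analysis should keep every ED.

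Four stronger readings are tempting and not supported:
- **The excess is confined to centre 15.** Table J2 has intervals above zero for centres 1 and 12 as well, and centre 11 is at +3.3 points. Their excesses are real in the table but offset by deficits elsewhere.
- **The result reverses.** The estimates without centre 15 run from -0.17 to about 0.00, and both computed intervals span zero.
- **No ED-versus-community excess survives.** Table J3 does not depend on centre 15.
- **Centre 15 under-recorded in its control period** (19 diagnoses against 80 in the intervention period, Table H1). Control-period data do not enter Table J1. A rate for that period would need an adult denominator that is not tabulated by centre, and timing within a changing epidemic is an equally ready explanation.

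**Conclusion.** The point holds for Table J1 and no further. The net excess of +0.63 points with all EDs (+0.52 matched by department) becomes -0.17, about 0.00 or -0.05 without centre 15, depending on the comparator. No other single ED has this effect. The data therefore do not support a general ED excess in asymptomatic/paucisymptomatic screening, and they do not show a deficit either.

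The result rests on the Table J2 counts being correct. Step 4 also assumes that centre 15's department tests are contained in the Table J1 total. The intervals are the plan's own Miettinen-Nurminen intervals, which make no allowance for clustering by ED. The primary outcome is untouched. Nothing in the documents reviewed generalises Table J1 to all EDs; the risk lies in a reader doing so from the pooled figure and the section 2.2 expectation.

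**What to change.** Keep all 18 EDs in the main comparison. In Changes to the analysis plan, Secondary endpoints analyses, add two sensitivity analyses for the nurse-driven screening comparison: (a) a leave-one-centre-out table in the format of Table I6; (b) an observed-against-expected difference with each ED matched to its own department (224 against 201.9, +0.52 points). Label both as added after the results were known.

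Beside Table J1, state that the net excess disappears without centre 15, that several other EDs have excesses offset by deficits elsewhere, and that a general ED excess in this screening is not supported. Report Table J3 separately.

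Cost: one table from counts already in Table J2, no new data, and a less favourable sentence in the report.
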